#### Control arm

Patients in the control arm (usual care) will receive the same HBPT device and BP measurement training as those in the intervention arm and will also follow the same measurement protocol—That is, 2 measurements taken in the morning and 2 taken again in the evening for 7 consecutive days. The values from the first day will be discarded and the mean SBP for the week will be computed from the average of the readings from the following 6 days, that is, 24 measurements. However, the study case manager will not interact with patients in this group. Patients in his group will be expected to inform their PCP or nurse practitioner (NP) of their BP readings at their scheduled consultations. For those in this group whose 6-day average SBP readings are ≥ 220/110 mmHg or <70 mmHg, the case manager will notify the Data Safety and Monitoring Committee (DSMC) for urgent review, treatment plan and referral strategy. Each participant’s PCP / NP will be informed of the patient’s involvement in the trial and will receive a letter with a copy of the study synopsis and 1-page guideline summary for BP thresholds, targets, and treatments relevant for CKD.

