### Outcomes

The primary outcome will be the mean difference (MD) in home SBP at 12 months, from baseline values. Secondary outcomes will include (1) proportion of patients with SBP within guideline target at end of the study, from baseline; (2) Proportion of patients who remained within target SBP throughout the study; (3) user acceptability of HBPT for BP control; (4) cost-effectiveness and cost utility of HBPT combined with a protocol-based case management approach, and (5) adverse events reported.

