### Sample Size Estimation

The sample size calculation for this trial is based on the data from HBPT plus pharmacist management trial on the hypertension population.^
22
^ Adequate power will be used to detect a clinically important absolute difference in mean SBP of 10 mmHg between the intervention arm and the control arm (usual care). Using a 2-sample t-test, alpha of 0.05 and power of 0.80, and assuming a common standard deviation of 19 mmHg, the required sample size will be ~58 patients per arm, or 116 in total. Accounting for ~20% attrition over 1 year, we will recruit 73 patients per arm, for a total of 146 patients. This sample size is also powered to detect a difference of 20% in the proportion of patients who maintain the guideline target of SBP (alpha 0.05, power 80%, and assuming event occurs 50% in the control group).^
22
^

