### Plan for Data and Statistical Analysis

Baseline statistics and the outcome variables will be described using counts and proportions, mean (SD) or median (interquartile range) as appropriate. All analyses will follow the intention-to-treat principle. We will estimate the effect size as the mean difference of SBP between groups at 12 months using a mixed linear-regression model include fixed-effects term for time point (6 months and 12 months), intervention, their interaction, and a random-effect term for participants. For the dichotomous outcomes (patients who maintained the SBP guideline and adverse outcomes), we will use Poisson regression with robust error variance to test the effect of the intervention.^
50
^ Continuous outcomes without repeated measurement will be examined using linear regression. We will adjust for eGFR for all the analyses. All estimated effect sizes will be reported along with 95% confidence intervals, and P<0.05 was considered statistically significant. We will analyze the data using Stata/MP 17.0 software (www.stata.com).

We will use multiple imputation method for missing data. Imputation of missing SBP values will only apply in instances when participants do not have any blood pressure recordings for the entire week. We will impute the missing SBP within each randomized group using age and sex separately at 6 months and 12 months. Estimate from each imputed data set will be combined using Rubin’s method.^
51
^ No interim analyses are planned due to the short duration of the study. However, for subgroup analysis, we will use the model from the analysis for primary analysis to explore the relationship between intervention and eGFR groups, age groups, the presence of diabetes, and so on.

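### Imputing 12-month SBP from age and sex, without the patient's own earlier SBP or eGFR, leaves the primary contrast open to bias if dropout depends on SBP differently by arm

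*Protocol article*

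**What the plan says.** All of this stands in the Protocol article, mostly under Plan for Data and Statistical Analysis.

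- Method: "We will use multiple imputation method for missing data".
- Predictors and structure: "We will impute the missing SBP within each randomized group using age and sex separately at 6 months and 12 months".
- When it applies: "Imputation of missing SBP values will only apply in instances when participants do not have any blood pressure recordings for the entire week".
- Primary model: a linear mixed model with "fixed-effects term for time point (6 months and 12 months), intervention, their interaction, and a random-effect term for participants".
- Covariate: "We will adjust for eGFR for all the analyses".
- Endpoint, under Outcomes: "The primary outcome will be the mean difference (MD) in home SBP at 12 months, from baseline values".

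Sample Size Estimation plans for about 20% attrition, 73 patients per arm, an SD of 19 mmHg and a "clinically important absolute difference in mean SBP of 10 mmHg between the intervention arm and the control arm". Design, Randomization, and Allocation makes the trial open label. Under Control arm, the case manager has no contact with control patients.

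**The concern.** An imputation model should contain at least the variables in the analysis model and the strongest predictors of the missing value. Here those are the patient's baseline SBP, SBP at the other visit and eGFR. The stated model has none of them.

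The mixed model does not repair this. After imputation the 6- and 12-month data are complete and balanced, so (before eGFR adjustment) the 12-month contrast is simply the difference between the two 12-month means. Those means include values drawn without reference to the patient's history. The same mixed model fitted to the observed data would let the 6-month SBP of a patient lost by 12 months inform the estimate, through the participant effect. The imputation step discards that information.

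At stake is the primary estimate. If uncontrolled control patients leave, or well-controlled case-managed patients stop transmitting, the imputed values do not reflect it, and the article describes no missing-data sensitivity analysis that would show it.

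**Working it through.** **The article's own figure.** Normal approximation: n = 2 × 19² × (1.960 + 0.842)² / 10² = 56.7, so 57 per arm. The exact two-sided t calculation gives 58 (power 0.802). Then 58 / 0.80 = 72.5, so 73 per arm and 146 in total. The sample size reproduces and is not affected by this point.

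**Inputs.** From the article: SD 19, effect −10 mmHg, 20% missing, 73 per arm. Assumed: equal between-visit correlation ρ of 0.4 to 0.7 (0.5 to 0.6 as the central case); age correlated about 0.15 with baseline SBP; dropout log-odds slope of 0.3 or 0.7 per SD of 6-month SBP.

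**Bias formula.** Let p be the fraction missing at 12 months and G the missing-minus-observed gap in mean 6-month SBP within an arm. The missing 12-month values differ from the observed ones by about ρG. Age and sex carry little of that gap, so imputation puts the missing group near the observed mean, and the arm mean is off by −pρG. For intervention minus control:

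bias ≈ p × ρ × (G control − G intervention)

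In simulation, slope 0.3 gives G of about 5.6 mmHg and slope 0.7 gives about 12.3 mmHg.

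| ρ | One arm, slope 0.3 | One arm, slope 0.7 | Opposite directions, slope 0.7 |
|---|---|---|---|
| 0.4 | 0.2×0.4×5.6 = 0.45 | 0.2×0.4×12.3 = 0.98 | 0.2×0.4×24.6 = 1.97 |
| 0.5 | 0.56 | 1.23 | 2.46 |
| 0.6 | 0.67 | 1.48 | 2.95 |
| 0.7 | 0.78 | 1.72 | 3.44 |

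Large-sample simulation of the age-and-sex imputation agrees. At slope 0.7, for ρ = 0.5, 0.6 and 0.7, control-only dependence gave 1.20, 1.46 and 1.71 mmHg, and opposite dependence gave 2.44, 2.93 and 3.41. Intervention-only dependence gave −1.23, −1.47 and −1.70, so the sign depends on which patients leave. With the same dependence and 20% dropout in each arm, bias was within 0.02 mmHg at ρ = 0.6 and 0.7. If one absolute-SBP rule makes the dropout rates differ, it was 0.1 to 0.8 mmHg (slopes 0.3 to 1.0).

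**Equivalence with complete cases.** At ρ = 0.6, control-only dependence gave −8.48 for complete cases and −8.48 for age-and-sex imputation. Opposite dependence gave −6.99 and −7.01. The true difference was about −9.94 in both.

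**At 73 per arm, ρ = 0.6, slope 0.7:**

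| Dropout depends on 6-month SBP | Age and sex: mean / coverage / power | Baseline and 6-month SBP added: mean / coverage / power |
|---|---|---|
| Equally in both arms | −9.95 / 94.3% / 0.80 | −10.01 / 94.3% / 0.82 |
| Intervention arm only | −11.56 / 92.4% / 0.89 | −10.04 / 95.1% / 0.84 |
| Opposite directions | −7.05 / 87.1% / 0.52 | −10.10 / 94.7% / 0.83 |

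Further simulations with correlations 0.5 (baseline to 6 months), 0.5 (baseline to 12) and 0.6 (6 to 12) gave 3.0 to 3.5 mmHg for opposite dependence, with coverage down to 82%.

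**Precision under random dropout.** With those correlations, baseline and 6-month SBP explain R² = (0.25 + 0.36 − 2×0.5×0.5×0.6) / (1 − 0.25) = 0.31/0.75 = 0.413 of the 12-month variance. The standard error without them is larger by 1/√(1 − 0.2×0.413) = 1.044. Simulation gave 3.60 against 3.44, a ratio of 1.047.

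**The case against.** The strongest reply is that the between-arm difference is not biased merely because each arm mean is. If dropout depends on SBP equally in both arms at equal rates, the errors cancel; and if it is random there is none. No passage says that dropout will differ by arm. That stands. A reader might infer that the primary estimate is biased under any missing-at-random dropout, and the documents do not support that. What they do support is that the mechanism is plausible: open label, with active management in one arm only.

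A reader might also expect a bias above 4 mmHg. That needs opposite dependence with a log-odds slope near 1.0, which nothing in the article suggests.

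Nor should the whole precision gain be credited to imputation. Richer imputation alone takes the standard error from 3.60 to about 3.44. The further drop to about 3.08 comes from adjusting the analysis for baseline SBP, which is a separate choice.

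The statistical analysis plan is not shown and might add auxiliary variables. But the article states the predictors and the visit-by-visit structure as a rule, so this is not detail simply left to that plan.

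Finally, imputation is triggered by a week with no recordings at all, while under Control arm "The values from the first day will be discarded". A patient with first-day readings alone would have no usable value and, as worded, no imputed one. This should be rare, the mixed model tolerates a missing visit, and it is a minor matter of definition.

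**Conclusion.** The point holds in conditional form. As stated, the imputation adds no protection over complete cases and gives up information that the planned mixed model could use. The size, against a 10 mmHg target, is:

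- about 0 if dropout is random or equally SBP-dependent in both arms at equal rates;
- about 0.5 to 1.7 mmHg, in either direction, if it depends on SBP in one arm only (slopes 0.3 to 0.7);
- about 2 to 3.5 mmHg if it depends in opposite directions (slope 0.7);
- a standard error about 4 to 5% too large even under random dropout.

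These figures rest on the article's SD and attrition and on assumed correlations and dropout slopes. The ends of the bias ranges come from correlations of 0.4 to 0.7; at 0.5 to 0.6 the formula gives about 0.6 to 1.5 and 2.5 to 3.0 mmHg. The point should be fixed before analysis. It does not invalidate the design or the sample size.

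**What to change.** Either of two changes is enough.

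1. Impute 6- and 12-month SBP jointly, within arm, from baseline home SBP, the other visit's SBP, baseline eGFR, age and sex. In the large-sample simulations, adding baseline and 6-month SBP brought the bias to at most 0.04 mmHg. At 73 per arm, coverage was 94 to 97% and power 80 to 85%.
2. Drop the imputation and fit the likelihood mixed model, with baseline SBP included, to all observed 6- and 12-month data.

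While the text is open, define a missing series as one with no usable reading once the first day is removed. The variables are already collected, so the cost is analysis-plan wording and a few lines of Stata code.

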### Data Monitoring and Quality Assurance

Data will be entered directly at the site of data collection using laptops and an online REDCap database application. REDCap uses a secure syncing process and robust data validation techniques. The statistician will create REDCap reports that tabulate accrual, withdrawals, fully completed protocols numbers and create quality assurance queries. The study coordinator will run these reports and queries and then follow-up with the pertinent study personnel or participant.

### Ethics and Privacy Statement

Ethics approval for this study has been obtained from the University of Alberta Research Ethics Committee (#PRO00095231). To ensure patient confidentiality and that all collection, retention, use or disclosure of data complies with privacy legislation and ethical requirements, all personal identifiers will be removed from the research data repository.

### Integrated Knowledge Translation Strategy

TIKO is a collaborative project among researchers, knowledge users, and patient stakeholders. Relevant stakeholders have been involved from the project’s inception to ensure that it addresses the needs of patients and practitioners. We will provide quarterly updates tailored to each of the stakeholder groups (ie, policy briefs and fact sheets for policymakers, and infographics containing key messages for patients and PCPs). Our patient partners will contribute feedback that will inform the implementation of the intervention and will be instrumental in disseminating study updates and results to patients, care providers, and policymakers. To ensure the support required for patient and other stakeholder collaboration in this work, we will leverage the resources available from the Alberta SPOR Network. Adherence to the guiding principles for patient engagement in health research (inclusiveness, support, mutual respect and team building) will ensure that participation is mutually beneficial for all members of our research team.^
52
^

## Discussion

The key deliverable of this proposal is the generation of evidence that would allow targeted and effective population-level strategies to be implemented to improve health outcomes for high-risk hypertensive CKD patients in Canada’s rural and remote communities. Specifically, this work will: (a) reduce under-treatment, thereby slowing progression to ESKD and preventing CV disease; (b) reduce over-treatment and associated adverse consequences (eg, syncope, falls, worsening renal function); and (c) demonstrate proof-of-concept and provide the basis for developing relevant policies and knowledge translation strategies to enhance the uptake of findings in chronic disease contexts beyond CKD. Our findings will inform guidelines specific to the management of CKD and support policy recommendations that can be scaled to other high-risk population groups and chronic disease domains.

This proposal focuses on a high-risk population subgroup characterized by a large care gap and identified by PCPs as a priority—namely, patients with CKD and uncontrolled BP. The proposed intervention technology is eminently simple and feasible, and it represents a low-risk endeavor with high potential for a good return on investment. Moreover, leveraging on a team that includes all key players (patients, decision makers, PCPs and researchers) involved in the design and implementation of a pragmatic intervention further improves the feasibility of this study. The involvement of relevant clinical program leaders underscores the potential for broad implementation of key findings, policy partner buy-in, and scalability. Within the first 6 months, we will hire personnel, develop the case report forms, set up the telemonitoring process and web portal, perform on-site pilot testing and refine the processes. Patient recruitment will begin after 6 months and timelines to meet all study objectives are shown in Figure 5.

**Figure 5. fig5-20543581221077500:**
[figure not shown]
Timeline and milestones.

### Potential Challenges and Mitigation Strategies

We have identified potential challenges to this study and have prepared mitigation strategies to address them. First, although the 1-year follow-up period could be considered short, however, longer follow-up period is often desirable when observing hard outcomes (eg, progression to dialysis, time to first / repeat CV event, death, etc.). This follow-up duration was selected as we recognize that BP is a surrogate outcome and is the most important measure for predicting adverse CKD outcomes. Also, it is well established that reducing high BP among patients with CKD substantially reduces complications and risks of adverse events. Avoiding low BP and resultant adverse effects is also important. However, beyond the scope of this study, we will examine how treatment and monitoring affect hospitalization rates, CV events, and mortality over long term. Second, possible technological pitfalls may provide challenges to conducting this study. We note that frequent monitoring and intervening too aggressively may also cause adverse consequences. Such consequences will be minimized by responding to qualitative feedback, standardizing telemonitoring frequency, ensuring careful monitoring for adverse effects and changing drug regimens as necessary. Third, owning a smartphone and having access to wireless internet is an eligibility requirement for this study and could therefore exclude potentially eligible patients who do not have smartphones. However, as more than 85% of Canadians own a smartphone^
53
^ and have access to the internet, we do not expect that this will constitute a major barrier with recruiting participants in this study. However, it is anticipated that this proportion could be lower in the remote setting of our study and could provide a challenge to the execution of this study. In such instances, the study team will provide a smartphone and internet access to such patients. Fourth, poor access to medications, reluctance to titrate mediations despite telemonitoring and access to urgent care could also prove challenging. However, the steps we have highlighted for reviewing transmitted BP recordings and steps for referral should mitigate these challenges. Finally, operational costs could provide challenges and similar trials have proven expensive because of the cost of home BP monitors. However, we will minimize cost through use of simple, inexpensive devices and focusing on data relevant to the study’s objectives.

